### Quality of life

Quality of life is a major consideration in care of people with RCC and is a key component of this trial, which aims to explore the impact on QoL of a DFIS strategy compared to a CCS. The use of averaged QALY as a co-primary endpoint of the trial exemplifies the importance of this. QoL will be assessed with the following questionnaires: FACT-G (28 items in four domains)
[18], the FKSI-15 (15 items)
[19] and the EuroQol instrument (including EQ-5D^TM^ descriptive system and the EQ visual analogue scale, EQ-VAS)
[20].

Extensive QoL data were collected as part of the pivotal sunitinib trial programme
[21,22], including both generic measures (FACT-G, EQ-5D^TM^/EQ-VAS) and disease-specific measures (FKSI-15 and FKSI-DRS subscale), but the reporting of the EQ-5D^TM^/EQ-VAS data in the publication was restricted to baseline mean and standard deviations (sd) and modelled average for all follow-up. In addition, QoL data from patients who stopped treatment were not included in the analysis. As a result these data are of limited use for estimating the QALY gains from a sunitinib DFIS strategy in the NHS. A small Japanese trial
[23] reported baseline and follow-up EQ-VAS data for day 1 and day 28 of each treatment cycle. These data, plotted graphically, show a sawtooth pattern of QoL whilst taking sunitinib, with highest measures on day 1 and lowest measures on day 28, consistent with clinical experience. The authors report that the same pattern was seen in the EQ-5D^TM^ data, providing reassurance that both these instruments will be sensitive to identify the hypothesised benefit. This intra-cycle variability necessitates frequent QoL measures to accurately capture the information required and hence to maximise the opportunity to identify any QoL/QALY differences between the arms. This drives the timings of QoL data collection.

Information will be collected at clinic visits at baseline, and day 1 of sunitinib cycle 1, 2, 3 and 4. Administration in clinic will enable patients to be supported in their completion, if required, prior to initiation of postal questionnaires. After this timepoint EQ-5D^TM^/EQ-VAS information (a simple 2 page assessment) will be completed every 2 weeks by patients at home, over 18 weeks. At clinical assessment visits the FSKI and FACT-G will continue to be completed 6 weekly. It is the period when CCS arm patients continue treatment and most patients on the DFIS arm stop treatment (i.e. after 6 months), when QoL differences are predicted to be greatest and hence this is when QoL data collection is most intensive. After the intensive collection has finished, collection of all information (including EQ-5D/VAS) will revert to 6 weekly in clinic.

### Health economics

The relative cost-effectiveness of a sunitinib DFIS compared to a sunitinib CCS is another important endpoint in the STAR trial. Treatment strategies that reduce the total quantity of sunitinib administered whilst maintaining total health gain are likely to be significantly more cost-effective than the current standard treatment strategy, thus supporting the DFIS model. The potential QoL gains along with the potential reduced rates of adverse events due to treatment interruption make the use of a DFIS strategy worthy of additional investigation as a cost-saving strategy.

To enable a comprehensive cost-effectiveness analysis, information will be collected on community, primary, secondary and tertiary health care utilisation and third sector care of participants. This will be collected via MRU questionnaires and CRFs at each clinical review. The economic evaluation will consider both the NHS and Personal Social Services (PSS) perspective and a societal perspective. The latter will include out-of-pocket expenses, and the productivity costs to the patients and formal and informal care providers. The analysis will estimate the expected incremental cost per QALY of a sunitinib DFIS compared to a sunitinib CCS.

The extensive QoL data collected in this trial represents a unique source of information valuing health at every point of time. Using each follow-up collection point, the distribution QALY gains will be precisely plotted over time and compared between the two arms (co-primary endpoint of the overall trial). There is uncertainty regarding the utilities of different health states in advanced RCC; i.e. the value of ‘Q’ in the QALY, for example NICE report a range for utility values 0.6 to 0.8 for stable/progression free disease states
[4,24]. The results of this trial will answer questions about the risks and benefits of structured treatment interruption (DFIS) and will hopefully allow robust conclusions to be drawn. The uncertainty around the appropriate utilities for specific health states will be examined within a probabilistic sensitivity analysis and using scenario analyses where alternative EQ-5D algorithms are used to attach utilities to specific health states. An interim analysis between stages A/B and C of the QALY data collected will be used to ensure the assumptions used to power the trial on a QALY endpoint are correct. The decision analytic cost effectiveness model will also be used to estimate a value of information analysis (VoI)
[25] and provide a methodological framework that explicitly considers the uncertainty surrounding the decision of a health care system to adopt a new technology using the expected value of perfect information (EVPI).

### Statistical methods and analysis

Statistical analysis will be the responsibility of the STAR CTRU Trial Statistician. A full statistical analysis plan will be written before any formal analyses are undertaken.

All non-inferiority analyses will be conducted on both the ITT and per protocol analysis populations. For the superiority endpoints the ITT analysis will be given primacy, however for the non-inferiority endpoints equal weighting will be given to both the ITT analysis and the per-protocol analysis, as the ITT is likely to be the least conservative approach when testing for non-inferiority. An overall two-sided 5% significance level will be used for all superiority endpoint comparisons, and a one-sided 2.5% significance level will be used for all non-inferiority endpoints.

A formal interim analysis will take place after stages A and B (at 21 months after the start of recruitment). A feasibility and efficacy stopping rule have been specified (as detailed below) to ensure the trial is stopped as early as possible in the case of insufficient recruitment (Stage A) or insufficient efficacy (Stage B) in the DFIS arm. The DMEC in light of this interim data will make their recommendations to the Trial Steering Committee who will in turn decide whether the trial can continue to Stage C.

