### Intervention

Participants in both arms of the trial will receive sunitinib which will be administered orally at 50 mg once daily on days 1 to 28 of the standard 42 day cycle. Daily doses may be modified for toxicity to 37.5 mg and 25 mg, in line with standard clinical practice.

After completion of at least 4 cycles of sunitinib and maximal radiological response, participants will take up their randomisation arm. Participants randomised to the control arm will continue sunitinib according to the CCS i.e. continuing treatment until evidence of disease progression or toxicity precluding continuation. Participants randomised to the experimental arm will continue according to the DFIS i.e. they will temporarily stop sunitinib (a planned treatment break). Participants will remain off treatment until radiologically-confirmed evidence of disease progression. At this time sunitinib will be restarted following the same scheduling and dose as before. In participants who regain further disease control, after completion of a minimum of 4 cycles of sunitinib and maximal radiological response, further planned treatment breaks will be implemented.

All participants will continue with their allocated sunitinib treatment strategy as per protocol (with dose reductions as required) until radiologically-confirmed disease progression occurs whilst taking sunitinib, unacceptable toxicity or participant choice to stop per protocol treatment

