#### Stage B

An interim efficacy endpoint has been included to further ensure the appropriateness of extending recruitment and continuing the trial to stage C. PFS is not an appropriate comparator endpoint in the trial as, due to planned treatment breaks, the initial PFS is likely to be shorter in the DFIS arm compared to the CCS arm. TSF will be analysed (targeted to look at differences in 15 months strategy failure rates) in both arms and non-inferiority will be required to be demonstrated between the arms for the trial to continue to stage C. The TSF in the DFIS arm must be less than 15% worse than in the CCS arm (strategy failure assumed to be 80% at 15 months). Assuming 21 months of accrual and immediate analysis, 80% power, and assuming proportional hazards, this would require 67 events and a population of 112 patients (56 in each arm; approximately 53% of the 210 in total that will be randomised) who take up their randomisation at 6 months.

During the formal interim analysis, an analysis of the utility data so far obtained will also be performed to revise the estimates of the power to detect the composite QALY endpoint and to evaluate possible refinements in the trial design as a result.

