### Endnotes

^a^TSF is defined as the time from randomisation until death; disease progression on sunitinib; disease progression in the DFIS arm during a planned treatment break assuming no further disease response or stabilisation on subsequent sunitinib occurs; participant requires use of a new systemic anti-cancer agent for RCC or significant clinical deterioration where deterioration is assumed to be due to renal cancer progression and not another comorbidity and deterioration sufficient to warrant cessation of sunitinib if on treatment or to preclude restarting sunitinib if on a treatment break on the DFIS arm, without it being clinicially appropriate to arrange radiological confirmation of the progression

^b^SPFI is defined as the sum of the intervals from the start of each treatment block with sunitinib, until radiological evidence of disease progression provided there has been some evidence of disease control prior to ongoing progression

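### Stage B is sized on patients who take up their strategy, but TSF and the ITT analysis run from randomisation, before the arms can differ; the gate's error rate and power depend on a choice the protocol does not make

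*Protocol article*

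**What the plan says.** All references are to the protocol article.

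- **Statistical methods and analysis:** "All non-inferiority analyses will be conducted on both the ITT and per protocol analysis populations". The two carry equal weight, because ITT is expected to be the less conservative. The level is fixed: "a one-sided 2.5% significance level will be used for all non-inferiority endpoints".
- **Stage B, margin:** TSF on DFIS "must be less than 15% worse than in the CCS arm", with "strategy failure assumed to be 80% at 15 months".
- **Stage B, sizing:** "Assuming 21 months of accrual and immediate analysis, 80% power, and assuming proportional hazards", the requirement is 67 events in 112 patients, described as "approximately 53% of the 210 in total that will be randomised) who take up their randomisation at 6 months".
- **Endnotes (a):** "TSF is defined as the time from randomisation until death" or one of several failure events. Randomisation is at baseline (Randomisation timing).
- **Intervention:** "After completion of at least 4 cycles of sunitinib and maximal radiological response, participants will take up their randomisation arm". A cycle is 42 days, so treatment is the same in both arms for at least 4 × 42 = 168 days, or 24 weeks.
- **Stage C, last paragraphs:** for TSF and OS, Kaplan-Meier differences and a Cox model are both reported, and the Cox model has primacy.

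**The concern.** If both arms receive the same treatment for 24 weeks, the hazard ratio over that period is 1 by design. A DFIS that is truly worse therefore cannot have proportional hazards from randomisation, yet the sizing assumes them. The sample size also describes one population (patients who reach the point of divergence), while the endpoint's clock and the ITT set describe another (everyone, from day 0). Failures before divergence carry no information about the strategies, and they pull the hazard ratio towards 1, which is the favourable direction for non-inferiority.

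At stake is the gate before a further 790 patients are recruited. Depending on how the per-protocol set is read, the gate is either too easy to pass or has much less power than stated.

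**Working it through.** **Inputs from the protocol.** Control failure is 80% at 15 months; the margin is 15 points; 210 patients are randomised 1:1; accrual takes 21 months with immediate analysis; the test is one-sided at 2.5%.

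**Assumptions not in the protocol.** Exponential control failure, uniform accrual, no loss to follow-up, divergence at exactly 24 weeks (5.52 months) or 6 months, and every failure-free patient taking up the strategy.

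**1. The plan's own figures.**
- Control hazard: λ = -ln(0.20)/15 = 0.1073 per month.
- Implied margin HR: ln(0.05)/ln(0.20) = 1.861; its log is 0.6213.
- Share with an event by month 21: 1 - (1 - e^(-21λ))/(21λ) = 0.603. Then 112 × 0.603 = 67.5, which matches 67. This counts time from randomisation over the whole 21-month window.
- 53%: S(6) = 0.20^(6/15) = 0.525, close to 112/210 = 0.533. So 112 looks like the number expected to be failure-free at 6 months, combined with an event fraction that starts at day 0.
- As a separate matter, 67 events fit 80% power at one-sided 5% (65 by Schoenfeld, 69 by Freedman). At the stated 2.5% the need is 82-87, and 67 events give 72%.

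**2. ITT events before divergence.** Expected events with no true difference: 210 × 0.603 = 126.6. Of these, 43.9 fall after 24 weeks, or 39.6 after 6 months. The share before divergence is 1 - 43.9/126.6 = 65%, or 1 - 39.6/126.6 = 69%.

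**3. ITT Cox pass rate at the 15-point margin.** For 95% failure on DFIS at 15 months, the hazard ratio after divergence at t0 must be (-ln 0.05 - λt0)/(λ(15 - t0)): 2.36 for 24 weeks, 2.44 for 6 months. Simulated trials (4,000-6,000 per setting, pass if the upper 95% limit is below 1.861) gave:

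| Setting | ITT Cox HR, average | ITT passes | Taken-up set passes | Both pass |
|---|---|---|---|---|
| 95% failure, divergence at 24 weeks | 1.39 | 39% | 0.3-0.5% | 0.3% |
| 95% failure, divergence at 6 months | 1.36 | 42-45% | 0.2-0.3% | 0.2% |
| HR 1.861 after divergence only | 1.24-1.26 | 60-65% | 2.4-2.8% | 2.5-2.6% |
| HR 1.861 from day 0 | 1.88 | 2.2% | - | - |

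The last row shows that the test holds its level when hazards really are proportional from day 0.

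**4. Size of the taken-up set at month 21.** Only patients randomised by month 21 - t0 can have reached t0.
- 24 weeks: 210 × (15.48/21) × 0.553 = 86 patients, 44 later events.
- 6 months: 210 × (15/21) × 0.525 = 79 patients, 40 later events.
- Power with no true difference is Φ(√(D/4) × 0.6213 - 1.96): 50% for D = 40, 54% for D = 44. Simulation gave 48% for divergence at 6 months, against 93% for ITT with all 210.

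A slower start makes this worse. With 54 patients in months 1-9 and 13 × 12 = 156 in months 10-21, those past 6 months number (54 + 78) × 0.525 = 69.

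**The case against.** **The protocol anticipates the direction of bias.** It says that ITT is likely to be the less conservative analysis and adds per-protocol with equal weight. A reader might take 39-45% as the gate's error rate. It is the rate for ITT alone. If per-protocol means taken-up patients, as the sizing suggests, and both must pass, the joint rate is about 3% or less. This stands as far as it goes. But the article does not define the set, and a patient who progresses at week 12 has followed the protocol. The definition may be in an analysis plan that is not shown; the mismatch in the sizing is in the article itself.

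**The margin is absolute.** Stage B targets the 15-month failure rate. A Kaplan-Meier difference on ITT, tested against 15 points, passed in only 3-4% of trials at the margin. This also stands: the inflation comes from the Cox model with a constant hazard-ratio margin. But the article gives the Cox model primacy and sizes under proportional hazards.

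**Stronger readings that the document does not support.**
- One might quote 60-65%. That applies HR 1.861 only after divergence and gives 91-92% failure at 15 months, which is inside the 15-point margin.
- One might infer that 47% never diverge. The 53% is a Stage B planning figure for take-up at 6 months.
- One might extend the problem to Stage C. There, with 900 evaluable patients and an assumed control 2-year OS of 53.3%, ITT passes in 2.0% of trials with a true 7.5-point deficit, and in 6.9% with HR 1.241 after divergence at 6 months. That is not material inflation.

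**Randomising at baseline is a reasoned choice,** and comparing strategies from randomisation is legitimate. The point does not dispute either.

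**Conclusion.** The inconsistency within Stage B is real. Proportional hazards from randomisation cannot hold for a DFIS that differs, and the 112 patients and 67 events belong to neither analysis: ITT has 210 patients and about 127 events, and the taken-up set has about 79-86 patients and 40-44 events. So the gate has one of two problems. If ITT decides, or if per-protocol keeps compliant early failures, the Cox analysis passes a DFIS at the 15-point margin in about 39-45% of trials. If taken-up patients must also pass, error is controlled but power is about 48-54%, not 80%.

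The sizes rest on the assumptions listed in the working and on reading the margin as HR 1.86; the direction does not depend on the exact values. The stakes are those of a go/no-go decision on which the DMEC advises and the Trial Steering Committee decides, not of the final efficacy claim.

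**What to change.** 1. Reconcile Intervention, Statistical methods and analysis, Stage B and Endnotes (a): name the one population, clock and margin (with its scale, absolute or hazard ratio) that decide the Stage B gate.
2. Define the per-protocol set explicitly, including whether it keeps compliant patients who failed before divergence.
3. Drop the assumption of proportional hazards from randomisation.
4. Beside ITT, report a landmark analysis of patients who are alive, failure-free and on sunitinib at the end of cycle 4, analysed as allocated, with the share reaching the landmark by arm.
5. Restate expected events and power for each analysis.
6. In Stage C, keep ITT from randomisation and state the expected size and power of the per-protocol analysis.

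No new data are needed, but the change has a price. The stated Stage B power becomes clearly less favourable, so the numbers or timing of the gate may have to be reconsidered. The landmark set is defined after randomisation under open allocation, and some patients diverge later than cycle 4 because maximal response is also required. The landmark analysis should not be the sole gate at month 21: at about 48-54% power it would stop an equivalent DFIS about half the time.

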#### Stage A

An essential part of any trial is ensuring that recruitment targets are met. This is formalised in the STAR trial, to ensure that the results can be delivered to time and target. To do this the recruitment per month during months 10–21 (inclusive) of recruitment will be determined; not utilising the initial 9 months which are allowed to enable site set up and familiarity with the trial. To continue the trial, a specific recruitment rate must be attained. The 95% CI for a recruitment rate of one patient per centre per month, with 13 centres for 12 months, is .85-1.15. Therefore a minimum of 0.85 patients per centre open and recruiting per month would be required i.e. 133 patients recruited over the 12 month period, assuming all 13 centres opened and commenced recruitment in a timely manner.

#### Stage B

An interim efficacy endpoint has been included to further ensure the appropriateness of extending recruitment and continuing the trial to stage C. PFS is not an appropriate comparator endpoint in the trial as, due to planned treatment breaks, the initial PFS is likely to be shorter in the DFIS arm compared to the CCS arm. TSF will be analysed (targeted to look at differences in 15 months strategy failure rates) in both arms and non-inferiority will be required to be demonstrated between the arms for the trial to continue to stage C. The TSF in the DFIS arm must be less than 15% worse than in the CCS arm (strategy failure assumed to be 80% at 15 months). Assuming 21 months of accrual and immediate analysis, 80% power, and assuming proportional hazards, this would require 67 events and a population of 112 patients (56 in each arm; approximately 53% of the 210 in total that will be randomised) who take up their randomisation at 6 months.

During the formal interim analysis, an analysis of the utility data so far obtained will also be performed to revise the estimates of the power to detect the composite QALY endpoint and to evaluate possible refinements in the trial design as a result.

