**Methods/Design:**

The STAR trial is an NIHR HTA-funded UK pragmatic randomised phase II/III clinical trial in the first-line treatment of advanced RCC. Participants will be randomised (1:1) to either a sunitinib CCS or a DFIS. The overall aim of the trial is to determine whether a DFIS is non-inferior, in terms of 2-year overall survival (OS) and quality adjusted life years (QALY) (averaged over treatment and follow up), compared to a CCS. The QALY primary endpoint was selected to assess whether any detriment in terms of OS could be balanced with improvements in quality of life (QoL). This is a complex trial with a number of design challenges, and to address these issues a feasibility stage is incorporated into the trial design. Predetermined recruitment (stage A) and efficacy (stage B) intermediary endpoints must be met to allow continuation to the overall phase III trial (stage C). An integral qualitative patient preference and understanding study will occur alongside the feasibility stage to investigate patients’ feelings regarding participation or non-participation in the trial.

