## Background

### Renal cell carcinoma

Renal cell carcinoma (RCC) constitutes only 3% of adult malignancies, but is the sixth leading cause of cancer-related death due to the lack of effective therapy for locally advanced and metastatic disease.

The strategy of targeting angiogenic pathways has produced positive results in advanced RCC. Tyrosine kinase inhibitors (TKIs), e.g. sunitinib and sorafenib, and monoclonal antibodies, e.g. bevacizumab with IFNα, have produced improvements in terms of progression free survival (PFS) and overall survival (OS). Sunitinib (Sutent™) selectively targets multiple protein receptor tyrosine kinases including vascular endothelial growth factor receptor and platelet-derived growth factor receptor. This inhibits tumoural delivery of blood and nutrients required for growth, which ultimately leads to cancer cell death. Sunitinib also has a direct inhibitory effect on tumour cells
[1].

The landmark sunitinib trial in RCC was a double-blind randomised controlled trial of 750 patients (ECOG performance status 0 or 1) with metastatic RCC which compared sunitinib to IFNα as first-line therapy
[2]. The primary endpoint was PFS and the trial was unblinded after a second interim analysis demonstrated significant benefit in patients treated with sunitinib. Updated results were published in 2009 and demonstrated a median PFS of 11 months with sunitinib and 5 months with IFNα in the intention-to-treat population (p<0.001)
[3]. The OS was 26.4 months with sunitinib and 21.8 months with IFNα (HR 0.821; 95% confidence intervals [CI]=0.673-1.001, p=0.051), however this difference is likely to be an underestimate due to significant crossover from IFNα to sunitinib after unblinding. Sunitinib was also associated with improved response rates over IFNα (47% vs 12%).

Sunitinib was approved by NICE in 2009 for UK use in the first-line treatment of advanced RCC in patients with a good performance status (ECOG 0 or 1) until evidence of disease progression or unacceptable toxicity
[4]. This was after reappraisal under the specific ‘end-of-life’ criteria as it had not previously been approved under standard NICE decision-making criteria.

Sunitinib is associated with a significant side effect burden. The landmark first-line trial reported that 19% of patients discontinued sunitinib due to adverse events (AEs) and 50% of patients required a dose reduction

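### Stage B: 67 events, 80% power and a one-sided 2.5% level do not fit together; at that level 67 events give about 72% power

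*Protocol article*

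**What the plan says.** Only the protocol article is at hand. It fixes the Stage B test as follows.

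- **Role of the test** (Stage B): "non-inferiority will be required to be demonstrated between the arms for the trial to continue to stage C".
- **Margin and control rate** (Stage B): TSF in DFIS "must be less than 15% worse than in the CCS arm (strategy failure assumed to be 80% at 15 months".
- **Power, accrual and model** (Stage B): "Assuming 21 months of accrual and immediate analysis, 80% power, and assuming proportional hazards".
- **Resulting size** (Stage B): "this would require 67 events and a population of 112 patients", that is 56 per arm.
- **Allocation** (abstract, Methods/Design): "Participants will be randomised (1:1) to either a sunitinib CCS or a DFIS".
- **Significance level** (Statistical methods and analysis): "a one-sided 2.5% significance level will be used for all non-inferiority endpoints".

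Stage B states no level of its own. The analysis paragraph under Stage C, which also covers the Stage B TSF comparison, plans 95% confidence intervals and gives primacy to the Cox model. A two-sided 95% interval compared with a margin is a one-sided 2.5% test, so it agrees with the general rule.

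**The concern.** The inputs to the Stage B calculation are all on the page, and at the declared level they do not lead to 67 events. Stage B decides whether the trial goes on to Stage C and its further 790 patients, so its operating characteristics should be those stated.

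If the test is run at one-sided 2.5% with 67 events, a DFIS that is truly equal to the conventional continuation strategy (CCS) fails it about 28% of the time, not 20%. If it is run at one-sided 5%, the chance of passing a strategy that sits exactly at the margin is twice the declared level. The two readings can also give opposite answers on the same data, as shown below. The data monitoring committee needs one rule before it sees the results.

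**Working it through.** **Inputs.** CCS failure is 80% at 15 months; the margin is 15 percentage points, so 95% failure in DFIS at the margin; power is 80%; allocation is 1:1; hazards are proportional; accrual lasts 21 months with immediate analysis (all Stage B or abstract). The level is one-sided 2.5% (Statistical methods and analysis). I assume a true hazard ratio of 1, the usual alternative when sizing a non-inferiority test; the article does not state it for Stage B.

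**Margin as a hazard ratio, DFIS over CCS.** ln(0.05)/ln(0.20) = 1.861, and ln(1.861) = 0.6213.

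**The plan's patient number, reproduced.** With exponential failure the hazard is −ln(0.20)/15 = 0.1073 per month. With uniform accrual over A = 21 months the hazard times A is 2.253, and the probability of an observed event is 1 − (1 − e^(−2.253))/2.253 = 0.603. Then 67/0.603 = 111.1, and 112 × 0.603 = 67.5. This matches 112 patients and indicates that the 80% input and the accrual are read as the authors used them.

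**Events needed.** Schoenfeld: d = 4(z_α + z_β)²/(ln HR)². Freedman: d = (z_α + z_β)²[(HR + 1)/(HR − 1)]².

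| One-sided level | z_α + z_β | Schoenfeld | Freedman |
|---|---|---|---|
| 2.5% | 1.960 + 0.842 | 81.3, so 82 | 86.6, so 87 |
| 5% | 1.645 + 0.842 | 64.1, so 65 | 68.2, so 69 |

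The stated 67 lies between the two formulas at 5% and well below both at 2.5%. Solving for the level that 67 events and 80% power imply gives 4.4% (Schoenfeld) to 5.2% (Freedman).

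**Power with 67 events at one-sided 2.5%.**

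- Schoenfeld: Φ(0.6213 × √67/2 − 1.960) = Φ(0.583) = 72.0%.
- Freedman: Φ(√67 × 0.861/2.861 − 1.960) = Φ(0.504) = 69.3%.
- At one-sided 5% the same formulas give 81.5% and 79.4%.

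A simulation with exponential failure, equal hazards and 21-month uniform accrual agrees: 112 patients gave 72.0% power at 2.5% and 81.3% at 5%, and 136 patients gave 79.8% at 2.5%.

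**Patients for 82 events.** 82/0.603 = about 136 who take up their allocation, against 112.

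**Other readings of the margin, at one-sided 2.5% (Schoenfeld).**

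- 80% to 65% failure-free: HR 1.931, 73 events. The event probability would then be about 0.141, so 67 events would need about 475 patients, which the stated 112 rules out.
- A relative 15% (80% to 92% failed): HR 1.569, 155 events.
- 65% to 80% failed: HR 1.533, 172 events.

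None gives 67.

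**Effect on the decision.** With 67 events the standard error of the log hazard ratio is about 2/√67 = 0.244. The largest observed hazard ratio that passes is exp(0.6213 − 1.960 × 0.244) = 1.15 at 2.5% and exp(0.6213 − 1.645 × 0.244) = 1.25 at 5%. A result between these stops the trial under one level and continues it under the other.

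**The case against.** The strongest defence is that one-sided 5% was meant for this phase II decision. It explains 67 almost exactly, and the sentence in the Stage C section that ties sample sizes to a one-sided 97.5% interval covers only overall survival and QALYs. The full protocol may state the Stage B level. This stands as an explanation of where 67 comes from. It does not remove the inconsistency, because the article applies 2.5% to all non-inferiority endpoints and plans 95% intervals for TSF.

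It is also fair that Stage B is an intermediate test, that the steering committee takes the final decision, and that if 2.5% is kept the false-positive rate is as declared. The loss is then about 8 points of power and nothing else.

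A reader might infer more than the document supports:

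- **That 67 is simply wrong and 82 is the right count.** The document shows that level, power and event count disagree. It does not show which was intended.
- **That 80% failure contradicts the landmark trial,** where the article says sunitinib "demonstrated a median PFS of 11 months with sunitinib". An exponential curve with that median would put failure at 15 months at about 61%. But PFS is not TSF, which also counts a new systemic agent and clinical deterioration without a scan. The Stage B count concerns patients who take up their allocation at about 6 months, not an intention-to-treat population. The two rates are not like for like.
- **That 112 should have been per arm,** because a comparison of 15-month proportions happens to give 112 per arm. Stage B is sized on events under proportional hazards, and 112 in total follows from 67/0.603. The match is probably a coincidence.

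**Conclusion.** The inconsistency is real and can be shown from the article alone. At the declared one-sided 2.5%, 67 events give about 72% power (69% by Freedman) instead of 80%, and 80% power needs 82 events (87 by Freedman). Rounding down to 81 would leave power at 79.8%, just short.

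This rests on a 15-point absolute margin, proportional hazards, equal true hazards and a single analysis. The article gives equal weight to the intention-to-treat and per-protocol analyses; if both must pass, power cannot exceed these figures. The patient numbers rest further on exponential failure and uniform accrual, which reproduce the plan's own 112. The point concerns only the agreement of level, power and event count in Stage B. The choice of margin and its scale are not in question here.

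**What to change.** Decide which of the three figures gives way, and say so before the Stage B analysis:

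1. **Keep 67 events and 112 patients at one-sided 2.5%,** and restate the power in Stage B as about 72%. Cost: one line and a less favourable figure.
2. **If one-sided 5% was intended,** state it in Statistical methods and analysis as an explicit exception for Stage B, and change the Stage B interval in the analysis paragraph under Stage C to 90% two-sided. Cost: two short edits, and an openly higher error rate for this decision.
3. **Keep 80% power at one-sided 2.5%,** and require 82 events before the analysis. Cost: 82 − 67 = 15 more events. At the plan's own event fraction that is about 136 − 112 = 24 more patients who take up their allocation. At its take-up of 112 in 210, that is 136 × 210/112 = 255 randomised instead of 210, or else a later analysis.
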